**Appendix 3. Overview of caregiver and patient outcomes and potential effect modifiers**

| *OVERVIEW* | Instrument | Items | Form | Time min | T0 | T1 | T2 | T3 | T4 |
| --- | --- | --- | --- | --- | --- | --- | --- | --- | --- |
| *Outcomes caregiver* |  |  |  |  |  | 6 m | 12m | 18m | 24m |
| Burden | SSCQ | 12 | I | 10 | X | X | X | X | X |
| QoL | MDS* & EQ5D |  | Q | 20 | X | X | X | X | X |
| Psychopathology | GHQ12 | 12 | I | 10 | X |  | X |  | X |
| Care utilisation, care time and absenteeism | MDSe* / cost diary |  | Q/I | 15 | X | X | X | X | X |
| *Outcomes pt* |  |  |  |  |  |  |  |  |  |
| Presence of dementia / MCI | CAMCOG1 |  | I | 25 | X |  | X |  |  |
| QoL | QoL-AD & EQ5D | 16 | I | 15 | X | X | X | X | X |
| Care utilisation etc. | MDSe* / cost diary by porxy |  | Q/I | 0 | X | X | X | X | X |
| Time until nursing home admission | According to carer or PCP | - | I |  |  |  | X |  | X |
| *Potential effect-modifiers / confounders* |  |  |  |  |  |  |  |  |  |
| Carer: |  |  |  |  |  |  |  |  |  |
| Sociodemography | MDS | 5 | I |  | X |  |  |  |  |
| Social support  Duration and intensity of caring | SSSL  Added Q | 8  1  1 | Q  I |  | X  X |  | X |  | X |
| Patient: |  |  |  |  |  |  |  |  |  |
| Sociodemography | By proxy | 5 | I | 5 | X |  |  |  |  |
| Dementia type | Medical Records | 1 | I | 0 |  |  | X |  |  |
| Morbidity | MDS by proxy | 1 | I | 5 | X |  |  |  |  |
| Behavioural symptoms | NPI | 12 | I | 10 | X |  | X |  | X |
| PCP / primary care practice:  - Age  - Sex  - Presence of practice nurse for elderly patients  - Interested in dementia  - % patients ≥ 65  - Cluster size | Q  Q  Added Q  Added Q  Medical rec | 1  1  1  3 | Q  Q  Q  Q |  | X  X  X  X  X  X |  |  |  |  |

I=Interview

Q=Questionnaire

MDS* / MDSe*: Minimal DataSet / Minimal DataSet cost-effectiveness respectively (NPO-ZonMW).

1 intervention arm only

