**Setting and Study population:**

The cluster RCT is executed in 16 primary care practices (PCPs) among 312 patients ≥ 65 years in whom FPs suspect cognitive impairment.

The diagnostic accuracy study is executed among 312 patients labelled ‘possible cognitive impairment’ and in 100 patients labelled ‘no signs of cognitive impairment’ by FPs.

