**Main study parameters**

Ad 1-2 (b) 23 quality indicators: 13 on the diagnostic process, 3 on follow-up care, 4 on structure of care and 3 on outcomes after 12 months.

(a) The number of MCI and dementia diagnosis after 12 months.

Ad 3. Patient: Quality of life (EQ5D, QoL-AD); mental wellbeing (MH5); worrying (…), information needs (…). Caregiver: mental health (GHQ 12); burden (SSCQ); quality of life (EQ-5D); worrying (..), information needs (…) over 12 months.

Ad 4. Diagnostic accuracy of FPs’ cognitive classification of individuals compared to the reference standard (CAMCOG) diagnosis at baseline.

**Nature and extent of the burden and risks associated with participation, benefit and group relatedness:** The interventions done within the context of the study are regarded to be of no risk to the patients and caregivers exposed to them. We aimed to minimise the burden placed on dementia patients and their caregivers by limiting the interviews with patients and carers (and questionnaires for carers) to twice a year.

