**Measurement**

- Patient and caregiver characteristics and outcomes (n =156)

- CAMCOG (n =156)

- Outcomes in patients with a baseline diagnosis MCI or dementia on the CAMCOG and their informal caregiver

(n ~ 156)

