## Multivariate analysis

We will do multilevel multivariate analysis to compare the two care conditions controlling for baseline imbalance and clustering effects within practices on number of incident diagnoses (goal 1), quality of care (goal 2) patient and caregiver outcomes (goal 3). Effect modification will be explored on principal characteristics (age, gender, severity dementia and type of caregiver). A post hoc analysis on main outcomes will be done on patients who score under critical cut off on CAMCOG at baseline (<86).

In addition, an economic evaluation is performed from societal perspective comparing the effects of goals 1 to 3 and costs in the two conditions. To compare costs between the two groups, confidence intervals for the differences in mean costs are calculated using bias-corrected and accelerated bootstrapping with 5000 replications. For the cost-effectiveness analysis the difference in total costs between the intervention and usual care group are compared with the difference in main clinical outcomes.

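### Appendix 3 restricts the CAMCOG to the intervention arm, although the accuracy study, Figure 2 and the post hoc analysis in section 9.3 need it in both arms

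*Protocol*

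**What the plan says.** **Appendix 3.** The row "Presence of dementia / MCI | CAMCOG1" has crosses at T0 and at 12 months (T2). The superscript 1 leads to the note "1 intervention arm only". No other instrument in the table carries that marker.

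**Accuracy study.** The Summary names the main parameter for goal 4: "Diagnostic accuracy of FPs’ cognitive classification of individuals compared to the reference standard (CAMCOG) diagnosis at baseline". It also states the sample: "The diagnostic accuracy study is executed among 312 patients labelled ‘possible cognitive impairment’ and in 100 patients labelled ‘no signs of cognitive impairment’ by FPs". Section 4.4 and the secondary endpoints in section 7.1 describe the same comparison. By section 4.4 the trial has 156 patients per arm, so the 312 are the whole trial sample from both arms.

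**Figure 2 (section 7.3).** The CAMCOG appears four times with n = 156. The figure also lists, twice, the follow-up group "Outcomes in patients with a baseline diagnosis MCI or dementia on the CAMCOG and their informal caregiver".

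**Section 9.3.** After describing the multilevel comparison of the two care conditions, it adds: "A post hoc analysis on main outcomes will be done on patients who score under critical cut off on CAMCOG at baseline (<86").

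Nothing in the protocol reconciles the footnote with these other places.

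**The concern.** Appendix 3 is the table that assigns instruments to time points, so field staff could reasonably follow it. If they do, control patients get no CAMCOG. A baseline measurement that was never taken cannot be recovered later, and no analysis plan can supply it.

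Three uses of the CAMCOG are then affected:

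- **Goal 3, wellbeing.** Figure 2 shows follow-up of patients with a baseline CAMCOG diagnosis of MCI or dementia, and research question 3 concerns diagnosed patients and their relatives. Without the test, that group cannot be identified among controls. The FP's own diagnosis is a poor substitute because the intervention is meant to change it. Section 4.4 plans on an earlier trial in which 49.1% of intervention patients and 14.8% of control patients were diagnosed. Selecting on that diagnosis would be selecting on something that happens after randomisation.
- **The analysis below 86.** It compares care conditions in a subset defined by baseline score, so both arms need the score.
- **Goal 4, accuracy.** Half of the FP-positive patients, and the practices they come from, would have no reference diagnosis.

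**Working it through.** **Inputs.**
- FP-positive patients: 312, and FP-negative patients: 100 (Summary; sections 3 and 4.4).
- Patients per arm: 156 (section 4.4).
- Assumed positive predictive value: 30%, with a stated confidence interval of 17.9% (section 4.4).
- Confidence level: not stated for this calculation; 95% two-sided is assumed here.

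**1. The number per arm.** Section 4.4 starts from 57 caregivers per group, about half of patients having a caregiver, 20% loss and 10% for clustering: 57 / 0.5 / 0.8 × 1.1 = 156.75. This agrees with the stated 156, and 2 × 156 = 312.

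**2. The plan's own precision figure.** The full width of a 95% Wald interval is 2 × 1.96 × √(p(1 − p)/n), with p = 0.30.
- n = 100: 3.92 × √(0.21/100) = 17.96 points, which matches the stated 17.9%.
- n = 312: 3.92 × √(0.21/312) = 10.17 points.
- n = 412: 8.85 points.

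The stated figure is therefore reproduced as a full width at n = 100, not at 312 or 412.

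**3. Positive predictive value if the footnote is followed.** FP-positive patients with a reference diagnosis: 312 − 156 = 156.
- n = 156: 3.92 × √(0.21/156) = 14.38 points.
- Ratio to the both-arm width: 14.38 / 10.17 = 1.41.
- Dividing n by 1.1, the clustering allowance used elsewhere in section 4.4, gives 10.7 points at 312 and 15.1 at 156. The comparison hardly changes.

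**4. Total accuracy sample.**
- Both arms tested: 312 + 100 = 412.
- Footnote followed, all FP-negative patients still tested: 156 + 100 = 256, a loss of 156/412 = 38%.
- Footnote also applied to FP-negative patients, assuming 50 per arm: 156 + 50 = 206, a loss of 50%. The protocol does not say that the footnote reaches this sample.

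**5. CAMCOG-defined groups among controls.** Control patients with a baseline score: 0 instead of 156. Neither the subset below 86 nor the follow-up group in Figure 2 can be formed in that arm, so no randomised contrast exists for either.

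**6. Dependence on Figure 2's layout.** The figure was flattened in the text available, so the assignment of entries to arms and times is inferred. Four entries of n = 156 fit two arms at two time points. The contradiction does not rest on this: 312 trial patients with a CAMCOG reference diagnosis cannot come from one arm of 156.

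**The case against.** The other side has real limits to set, and most of them stand.

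- **The primary outcome is not touched.** None of the 23 quality indicators in Appendix 2 uses the CAMCOG, and nothing ties the 12-month count of diagnoses to it. A reader might infer that the main comparison is lost; the protocol does not support that.
- **The analysis below 86 is labelled post hoc.** Its loss is not the loss of a main analysis.
- **The stated precision survives.** With 156 patients the width is 14.4 points, still inside 17.9.
- **The accuracy sample as a whole is not halved.** Only the FP-positive part is. Halving all 412 would require the footnote to cover the FP-negative sample as well.
- **Using one arm need not bias the predictive value.** FPs in both arms make the same classification (section 5.1), the comparison is at baseline, and practices are randomised. The harm is lost precision and lost practices.
- **Dementia severity as an effect modifier.** It is tempting to say this is lost in controls too. Section 9.3 does not name the CAMCOG as the severity measure, and Appendix 3 lists it under presence of dementia or MCI.
- **The status of Figure 2's follow-up group is unclear.** Its size is given as about 156, equal to a whole arm, and section 9.3 puts no CAMCOG restriction on the goal 3 analysis.

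The last point weakens the goal 3 consequence somewhat but does not remove it: Figure 2 names the group by baseline CAMCOG diagnosis and research question 3 concerns diagnosed patients. If the footnote is only a slip, it is still the instruction in the schedule. If it is deliberate, the accuracy sample, Figure 2 and section 9.3 are wrong.

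**Conclusion.** The protocol contradicts itself on who receives the CAMCOG. Following Appendix 3 leaves 0 of 156 control patients with a score. The post hoc comparison below 86 and the CAMCOG-defined follow-up group for goal 3 then cannot be formed in controls. The sample for the positive predictive value falls from 312 to 156, with the interval width at 30% rising from 10.2 to 14.4 points. The total accuracy sample falls from 412 to 256, assuming that all 100 FP-negative patients are still tested.

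The widths assume a 95% Wald interval without clustering. The consequences are conditional on staff following the schedule rather than Figure 2. The point is worth correcting before data collection because the loss of baseline data would be permanent. It does not extend to the primary outcome or to the precision that section 4.4 states.

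**What to change.** Delete footnote 1 for the CAMCOG in Appendix 3, so that the test is scheduled in both arms at T0 and 12 months, consistent with Figure 2, the accuracy study and section 9.3. If the note was meant for another instrument, move it there.

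The text change is one footnote. In the field it means a 25-minute interview item (Appendix 3) at two visits for control patients, which Figure 2 already appears to count. If the restriction was intended, the alternative is larger: the 312 in the accuracy study, the entries in Figure 2 and the subset in section 9.3 would all have to be rewritten.
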